## Abstract

**Background:**

Disturbed sleep is common among people living with dementia and their informal caregivers, and is associated with negative health outcomes. Dyadic, multi-modal interventions targeting caregiver and care-recipient sleep have been recommended yet remain limited. This protocol details the development of a single-arm feasibility trial of a multi-modal, therapist-led, six-week intervention targeting sleep disturbance in dyads of people living with dementia and their primary caregiver.

**Methods:**

We aim to recruit 24 co-residing, community-dwelling dyads of people living with dementia and their primary informal caregiver (*n* = 48) with sleep concerns (Pittsburgh Sleep Quality Index ≥5 for caregivers, and caregiver-endorsed sleep concerns for the person living with dementia). People who live in residential care settings, are employed in night shift work, or are diagnosed with current, severe mental health conditions or narcolepsy, will be excluded. Participants will wear an actigraph and complete sleep diaries for two weeks prior, and during the last two weeks, of active intervention. The intervention is therapist-led and includes a mix of weekly small group video sessions and personalised, dyadic sessions (up to 90 min each) over six weeks. Sessions are supported by a 37-page workbook offering strategies and spaces for reflections/notes. Primary feasibility outcomes are caregiver: session attendance, attrition, and self-reported project satisfaction. Secondary outcomes include dyadic self-reported and objectively-assessed sleep, depression and anxiety symptoms, quality of life, and social support. Self-report outcomes will be assessed at pre- and post-intervention.

**Discussion:**

If feasible, this intervention could be tested in a larger randomised controlled trial to investigate its efficacy, and, upon further testing, may potentially represent a non-pharmacological approach to reduce sleep disturbance among people living with dementia and their caregivers.

**ANZCTR Trial registration:**

ACTRN12622000144718: https://www.anzctr.org.au/Trial/Registration/TrialReview.aspx?id=382960&showOriginal=true&isReview=true

## Introduction

People living with dementia commonly experience changes to their sleep including frequent nighttime awakenings, daytime sleepiness and napping, changes in circadian functioning and “sundowning”—periods of agitation and disorientation commonly during the late afternoon and early evening (Elder et al., 2022; Wennberg et al., 2017; Ancoli-Israel et al., 1994). Some of these changes can be challenging, with over 70% of people living with dementia experiencing at least one type of sleep disturbance (Rongve, Boeve & Aarsl, 2010) including insomnia (Wennberg et al., 2017; Mayer et al., 2011), which is characterised by significant difficulties in initiating or maintaining sleep which cause distress and/or impact daytime functioning (American Psychiatric Association, 2013). There also is growing evidence that sleep disturbances and sleep disorders, such as insomnia, can increase the risk of developing all-cause dementia (Shi et al., 2018). Thus, treatment of poor sleep may be an important early prevention strategy for reducing the likelihood of future cognitive decline.

Sleep disturbances not only affect people living with dementia but those who support them at home (Gao, Chapagain & Scullin, 2019). In Australia, 91% of community-dwelling people living with dementia are informally supported by caregivers at home, many of whom are family members that provide 40 hours or more of informal care per week (Brooks, Ross & Beattie, 2015). While there is growing research into the positive aspects of caregiving (Quinn & Toms, 2019), caregivers commonly experience poor sleep. Over 91% of caregivers report poor sleep quality (Peng, Lorenz & Chang, 2019; Smyth et al., 2020), and one meta-analysis and systematic review found that caregivers reported significantly less sleep (up to 3.5 h loss per week) and had poorer sleep quality than non-caregiving age-matched peers (Gao, Chapagain & Scullin, 2019). Insomnia represents another concern among caregivers (McCurry, Song & Martin, 2015). In a recent study, 55% of caregivers report sleep onset latencies of over 30 min, with almost 20% who report times of over 60 min to fall asleep at night (Smyth et al., 2020). As the number of caregivers is projected to significantly rise over coming years (Brooks, Ross & Beattie, 2015), supporting unpaid caregivers through accessible ways represents an important area of research focus.

The underlying causes of sleep characteristics, such as poor sleep quality, in caregivers supporting people living with dementia are multifactorial. Caregiver demographic and psychosocial factors, as well as sleep-wake behaviours in the person they support can all increase the risk of disturbed sleep (Peng, Lorenz & Chang, 2019; Peng & Chang, 2013). For instance, poorer caregiver sleep quality has been associated with greater symptoms of caregiver stress, depression, and anxiety (Peng, Lorenz & Chang, 2019; Smyth et al., 2020; Van Hout et al., 2022) and predicts greater levels of fatigue (Chang et al., 2020). Additionally, sleep disturbances in people living with dementia have been strongly associated with greater levels of overload in caregivers (Gehrman et al., 2018), and are a key predictor of transition to formal residential care (Hope et al., 1998). This highlights the complex interplay of caregiver and care recipient sleep and wellbeing, which hold broader systemic implications.

Past studies have described how poor sleep in caregivers may be precipitated and perpetuated by sleep disturbances in the person they care for, such as tending to nighttime awakenings or wandering, but may not be fully explained by care recipients’ sleep (McCurry, Song & Martin, 2015; McCurry et al., 2008). Caregivers may engage in unhelpful sleep practices to compensate for disturbed nighttime sleep and daytime fatigue, such extending time in bed, daytime napping or using stimulants, which may consequently perpetuate experiences of poor sleep (Peng, Lorenz & Chang, 2019; McCurry, Song & Martin, 2015). Sleep disturbances in caregivers may also be maintained by stress, depression, and limited understanding of good sleep practices (Gao, Chapagain & Scullin, 2019; McCurry et al., 2007). From a cognitive behavioural perspective, this may place caregivers at a higher risk of developing and maintaining insomnia (McCurry, Song & Martin, 2015). Given the unique vulnerabilities to chronic sleep disturbance among those supporting people living with dementia at home, interventions that promote caregiver sleep health and daytime functioning are imperative, and may in turn improve the wellbeing and quality of care provided to those being supported.

Several interventions hold potential for improving sleep in caregivers and people with dementia (Table 1). Cognitive behavioural therapy (CBT) for insomnia is a non-pharmacological intervention that addresses unhelpful thoughts and behaviours associated with poor sleep; it improves sleep quality in general caregivers (Cooper et al., 2022; Fernandez-Puerta, Prados & Jimenez-Mejias, 2022), caregivers of people living with dementia (Gao, Chapagain & Scullin, 2019; Pignatiello et al., 2022) and people with mild cognitive impairment (O’Caoimh et al., 2019). Mindfulness-based interventions involve relaxation strategies and moment-to-moment awareness, which have been associated with reduced insomnia symptoms in caregivers (Jain, Nazarian & Lavretsky, 2014) and improved quality of life and mood in people with dementia (Hoffman et al., 2019). Light therapy involves appropriately-timed exposure to bright light to realign the circadian rhythm with externally required sleep/wake timing (Terman & Terman, 2011) and/or to reduce daytime sleepiness (Phipps-Nelson et al., 2003). Light therapy has been associated with significant improvements in circadian-related outcomes and sleep quality in caregivers (Pignatiello et al., 2022), with some sleep improvements in people living with dementia (O’Caoimh et al., 2019; Sidani et al., 2022). Similarly, physical activity interventions have been significantly associated with reduced sleep latency and greater sleep quality in caregivers (Pignatiello et al., 2022) and are associated with improved functional capacity in people living with dementia (Meyer & O’Keefe, 2018). Each of these interventions seem to have differential effects on sleep and daytime functioning (Table 1).

**Table 1 table-1:** Sleep and circadian interventions for caregivers and persons living with dementia.

**Intervention**	**Description**	**Summary of findings**
Cognitive Behavioural Therapy for Insomnia	A multi-component intervention that addresses unhelpful thoughts and behaviours associated with poor sleep Incorporates sleep education and sleep hygiene, combined with behavioural and cognitive components	Caregivers: Improvements in sleep quality (Cooper et al., 2022; Fernandez-Puerta, Prados & Jimenez-Mejias, 2022) Person living with dementia: Improvements in actigraphy-assessed sleep parameters (Poon, 2022)
Mindfulness interventions	Meditation training, relaxation strategies and moment-to-moment awareness	Caregivers: Reduced insomnia symptoms; improvements in sleep quality (Pignatiello et al., 2022; Jain, Nazarian & Lavretsky, 2014) Person living with dementia: Improved quality of life and mood (Hoffman et al., 2019)
Light therapy	Bright light therapy (BLT): • Involves the use of a light box placed at eye level, one meter in front of the patient. • Recommended dosage between 20 min to two hours in the morning. • BLT is conducted at least 5 days a week, over 10 days to two months, notably in winter times. Natural outdoor light exposure: • Spend time outdoors by walking or sitting during the recommended exposure time, or • Sit next to a window with open blinds during the recommended exposure time. • Recommended exposure time is 1 h in the morning around 9 a.m.	Caregivers: Improvement in circadian outcomes and sleep efficiency (Livingston et al., 2019; Song et al., 2021) Person living with dementia: Some evidence of improvements in objective and subjective sleep measures; but mixed findings across studies (Calvert et al., 2018) Small to moderate effect on circadian amplitude and night time awakenings/ sleep quality. Minimal effect on sleep duration and sleep efficiency (Sidani et al., 2022)
Physical activity interventions	Provide suggestions for engaging in daytime activities (*e.g.*, gardening, walking) Structured activities (*e.g.*, Tai Chi, resistance training)	Caregivers: Reduced sleep latency, improved sleep quality (Pignatiello et al., 2022) Person living with dementia: Improved functional capacity (Meyer & O’Keefe, 2018)

Recent systematic reviews have recommended *multi-modal* interventions that incorporate different therapeutic components (*i.e.,* cognitive and behavioural strategies, light therapy, exercise, mindfulness and relaxation) to comprehensively target determinants of sleep disturbance in caregivers and people with dementia (Pignatiello et al., 2022; O’Caoimh et al., 2019). Some studies have adopted a multi-modal approach to treating sleep disturbance in people living with dementia (see Poon (2022) for a review of these interventions and evidence of their efficacy) (Sidani et al., 2022; Livingston et al., 2019). In addition, *dyadic* interventions that jointly addresses poor sleep in both caregivers and care recipients have been recommended (Fernandez-Puerta, Prados & Jimenez-Mejias, 2022; Pignatiello et al., 2022). Dyadic interventions, in which both the caregiver and care-recipient are simultaneously targeted (Poon, 2022), present unique opportunities to concurrently target poor sleep in people living with dementia and those who informally support them. For example, caregivers may learn to facilitate healthy sleep practices in those they support while targeting their own sleep in tandem, thereby addressing precipitating and perpetuating factors of disturbed sleep more comprehensively.

In-home dyadic interventions may also be cost-effective; demands on external services may be significantly reduced given that sleep disturbance and daytime impacts are managed predominantly at home. However, with few exceptions (Song et al., 2021), efficacious, multi-modal, *dyadic* interventions for caregivers and people living with dementia with sleep disturbance remain limited.

The current article presents a protocol of a feasibility trial of a multi-modal dyadic intervention that is personalised, manualised, and group-based to target sleep disturbance in caregivers and people living with dementia. The intervention combines strategies from *cognitive-behavioural* and *mindfulness-based* strategies, *light therapy,* and *physical activity* for caregivers to address their own sleep concerns and support healthy sleep practices in the person they care for. The trial aims to assess program feasibility for caregivers (attendance and attrition rates, and satisfaction using Bowen criteria), and preliminary efficacy for improving sleep, quality of life, and wellbeing outcomes in the dyad.

## Methods

### Design

This is a single-arm feasibility trial (Fig. 1). Self-reported outcomes will be assessed at pre-intervention (T1, Week 0; within one week of intervention start date), post-intervention (T2; Week 6), and a Week 10 follow-up (T3). The primary endpoint is feasibility at T2. This protocol follows SPIRIT-PRO (Calvert et al., 2018) and TIDieR (Hoffmann et al., 2014) guidelines (see Supplementary). Due to the nature of the trial design, neither participants nor researchers will be blinded. Ethics approval was obtained by the Monash University Human Research Ethics Committee (30710).

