#### Intervention

After screening, eligible participant dyads will participate in a 20-minute “pre-orientation” session *via* video with a trained research assistant to explain use of actigraph and sleep diary, which are sent *via* post prior to predetermined start date. Participants will complete an online baseline questionnaire within a week prior to beginning the intervention; automatic prompts to complete all items will be provided, and email reminders will be sent if questionnaires have not been completed within five days of release*.* Eligible participants will receive the intervention as detailed below. Participants will wear an actigraph and complete sleep diaries daily for two weeks prior to intervention start date, and then return the watches and diaries to the research team to be downloaded and recharged. The actigraphs and new diaries will be posted to be worn again during Weeks 5 and 6 of the intervention. A trained research assistant will manage actigraph recharging and monitor data. Sleep diaries and actigraphs are returned following completion of the follow-up questionnaire (Week 10). Ethics approval will be sought by Monash University Human Research Ethics Committee for any protocol modifications before being implemented and communicated to participants if appropriate, and will be documented on a running sheet.

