#### Secondary outcomes

 1.*Sleep quality* measured by the PSQI, which has adequate reliability and validity in community samples with an internal consistency of *α* =.83 (Buysse et al., 1989). 2.*Sleep disturbance in people living with dementia* measured *via* the SDI. The SDI consists of seven items from the Neuropsychiatric Inventory sleep disturbance subsection (Cummings, 2020). Caregivers are asked to rate the frequency, severity and levels of caregiver distress associated with sleep-related behaviours displayed by the person in their care. 3.*Insomnia* symptoms measured by the Insomnia Severity Index (Bastien, Vallières & Morin, 2001). The ISI is a 7-item measure of self-reported insomnia symptoms. The ISI has been shown to have high internal consistency and a cutoff score of ≥8 has a sensitivity 96%–99% and specificity of 78%–92% in community and clinical populations respectively (Morin et al., 2011). 4.*Sleep-related daytime impairment* measured by PROMIS Sleep Related Impairment–Short Form–8a (PROMIS-SRI; Yu et al., 2011). 5.*Mood* measured by PROMIS Depression–Short Form–8a and PROMIS Anxiety–Short Form–8a (Pilkonis et al., 2011), both 8-item measures of depression and anxiety symptoms respectively, and the Depression, Anxiety and Stress Scales (Lovibond & Lovibond, 1995). 6.*Quality of life* measured by the EQ-5D-5L (Herdman et al., 2011) for caregivers and the Alzheimer’s Disease-related Quality of Life scale (Rabins et al., 1999) for people living with dementia. 7.*Objective sleep* measured *via* actigraphy. The actigraph (Actiwatch 2, Philips Respironics) is a small wrist-worn device resembling a wristwatch that incorporates an accelerometer, which detects body movement or lack of movement. Actigraphy data will be collected in conjunction with information from sleep diaries. An algorithm is then used to infer various sleep outcomes (*e.g.*, sleep onset, duration, time in bed) based on the absence of recorded movement. Although actigraphy does not measure sleep itself, the current algorithm of analyses made by these devices can provide feasible and valuable information about insomnia-related parameters and information related to circadian sleep-wake patterns that polysomnography is unable to provide (Krystal & Edinger, 2008). Actigraphy was verified using the Consensus Sleep Diary (Carney et al., 2012). Parameters used in the current study include: sleep onset latency in minutes, percentage of sleep efficiency, total sleep time in minutes, and wake after sleep onset in minutes.

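### The single-arm design does not justify leaving actigraphy processing unmasked to recording period (minor)

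*Protocol article*

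**What the plan says.** The Design section gives both a rule and a reason for it: "Due to the nature of the trial design, neither participants nor researchers will be blinded". No exception is made for staff who handle outcome data.

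The same section sets the primary endpoint: "The primary endpoint is feasibility at T2". Actigraphy sits among the secondary outcomes, which the abstract summarises as follows: "Secondary outcomes include dyadic self-reported and objectively-assessed sleep, depression and anxiety symptoms, quality of life, and social support".

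The Intervention subsection of Procedure describes two recording periods. For the first, "Participants will wear an actigraph and complete sleep diaries daily for two weeks prior to intervention start date"; devices and diaries then go back to the team for download. The second covers Weeks 5 and 6, and that material is returned after the Week 10 questionnaire. On handling, it says: "A trained research assistant will manage actigraph recharging and monitor data".

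Item 7 of Secondary outcomes says that an algorithm infers the sleep outcomes from the absence of movement. It also brings in the diary twice: "Actigraphy data will be collected in conjunction with information from sleep diaries" and "Actigraphy was verified using the Consensus Sleep Diary". The four parameters are sleep onset latency, sleep efficiency, total sleep time and wake after sleep onset.

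**The concern.** The reason does not support the whole of the rule. With one arm there is no allocation to conceal, so participants and therapists cannot be masked to treatment. A processor of recordings can still be masked to something else, namely the period a recording comes from.

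This matters because of what actigraphy is for in this trial. The other sleep, mood, quality-of-life and support measures are reported by participants or caregivers who know they have had the programme, and the Discussion itself notes a risk of bias from proxy completion. Actigraphy is the one sleep or efficacy measure that does not come from a questionnaire. The Statistical analysis section models all four parameters and reports Cohen's d, and the Discussion intends the limited-efficacy results to support a larger trial. If human judgement enters the processing and the processor knows the period, some of that independence is lost for no gain.

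**Working it through.** The plan states no figure on this point, so there is nothing to reproduce. The check is a reading of the sections together, followed by an illustration on assumed values.

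**1. Does the design prevent masking to period?** No. Each participant yields two recordings, one before the intervention and one from Weeks 5 and 6. These can be given neutral codes and shifted dates, and nothing in a single-arm design stands in the way.

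**2. Can judgement enter?** Absence of movement does not show when a person began trying to sleep. Sleep onset latency and sleep efficiency both need that time, and the diary is the only other source the article names. Where diary and movement disagree, a rule or a person has to settle it. The article describes no manual step, so a person doing so is a reasonable inference and not a documented fact.

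**3. Would an error have a direction?** Possibly. Table 3 shows that Session 1 teaches going to bed only once sleepy and keeping a steady wake time. A processor who knows that a recording is from Weeks 5 and 6 might expect later, tighter bed periods.

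**4. Illustration.** Assumptions, none of them from the documents: 480 min in bed, 400 min asleep, sleep onset fixed, and the start of the rest interval placed later by the same amount on every Weeks 5 and 6 night.

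Sleep efficiency = time asleep / time in bed × 100

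| Shift in rest-interval start | Calculation | Efficiency | Gain (points) | Change in onset latency |
|---|---|---|---|---|
| 0 min | 400/480 | 83.3% | – | – |
| 5 min | 400/475 | 84.2% | 0.9 | −5 min |
| 10 min | 400/470 | 85.1% | 1.8 | −10 min |

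Total sleep time stays at 400 min, and wake after sleep onset does not change because only the start of the interval moves. Two of the four parameters are therefore exposed to this particular shift. Selective exclusion of nights could affect any of the four, but nothing in the article allows that to be sized.

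**The case against.** The strongest reply is that the article describes algorithmic scoring and no hand editing. It does not say who scores the recordings or when, and a condensed article may leave such detail to the full protocol. That stands against any claim that bias is present. It does not rescue the blinding sentence, which is a stated decision with a stated reason, and the reason does not reach this far.

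A reader might infer four stronger things that the documents do not support:

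- *That actigraphy is the only objective outcome.* Attendance and drop-out are recorded counts and belong to the primary outcome. Actigraphy is the only sleep or efficacy measure that is not self- or caregiver-reported.
- *That the scorer always knows the period.* The research assistant is said to manage recharging and monitor data, not to score. Early download of the baseline device is not early or unmasked scoring.
- *That actigraphy is the only handle on expectation effects.* The Credibility Expectancy Questionnaire measures expectancy directly at T1.
- *That the trial's conclusion is at risk.* Primary outcome does list limited efficacy among the feasibility domains, but Statistical analysis judges feasibility on attendance, drop-out and caregiver satisfaction, none of which depends on scoring. The sample is a convenience sample of 24 dyads with no power analysis, and the abstract leaves efficacy to a later randomised trial.

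It is also fair to say that masking gives limited protection. Unmasked participants keep the diaries, and later, more regular bed times may themselves hint at the period. Larger threats to a before-after change remain: there is no control group, and selection on poor sleep invites regression to the mean. These cannot be removed within a single arm. Masking the processing can be done within it.

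**Conclusion.** The point holds as a minor one. The single-arm design justifies unblinded participants and therapists; it does not justify leaving actigraphy processing unmasked to recording period. Judgement in setting rest intervals, resolving diary-movement disagreement or excluding nights could lean toward improvement in Weeks 5 and 6.

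Whether it would do so, and by how much, cannot be learned from the documents. The range of about 1 to 2 points of sleep efficiency, with 5 to 10 minutes of onset latency, rests entirely on the assumed night and a uniform shift. It shows the mechanism and is not an estimate of bias in this trial. The primary feasibility assessment is unaffected.

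**What to change.** Limit the blinding sentence in Design to participants and therapists, and add wording such as:

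> Actigraphy is processed masked to recording period. A research assistant who does not run sessions replaces the labels and dates on each participant's two recordings and the matching diary bed and rise times with random codes and shifted dates. Both recordings are then processed in random order by someone else, under one fixed rule for disagreement between diary and movement and for excluding nights.

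Baseline wear-time checks and diary queries should still be done when the first device comes back, so that problems are raised with participants while memory is fresh.

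The cost is file relabelling by existing staff. Sample size, visits, measures and participant burden do not change. The main downside is delay: final baseline scoring has to wait for the second device and diary, which return only after the Week 10 questionnaire. Data collection is ongoing, but stored recordings can be recoded and reprocessed, and the article already provides an ethics route for protocol modifications. The trial report should still say that regression to the mean, the absence of a control group and unmasked diary-keeping limit what any actigraphy change can show.
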